### 2.8 Statistical Methods

Continuous data will be expressed as median and range. Categorical variables will be shown as frequency and proportion. Survival curves and cumulative incidence of LTP will be generated using the Kaplan-Meier method. The Cox proportional hazards method will be used for univariate and multivariate analyses to determine prognostic factors. Technical success, technique efficacy, nsPEF procedural characteristics, and local tumor progression will be analyzed per tumor. The rate of adverse events and local progression-free survival will be analyzed per patient. *P* values < 0.05 will be considered statistically significant. All statistical analyses will be performed with a software package (SPSS, version 23.0; SPSS, Chicago, Ill).

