## Abstract

**Background:**

Hepatocellular carcinoma (HCC) is a highly aggressive malignancy. Irreversible electroporation (IRE) is an ablative modality that uses high-voltage electrical pulses to permeabilize the cell membrane leading to cell necrosis. Unlike traditional thermal ablation, IRE is hardly affected by the “heat-sink” effect and can prevent damage of the adjacent vital structures. Nanosecond pulsed electric field (nsPEF) is a new IRE technique using ultra-short pulses (nanosecond duration), can not only penetrate the cell membranes, but also act on the organelles. Sufficient preclinical researches have shown that nsPEF can eliminate HCC without damaging vital organs, and elicit potent anti-tumor immune response.

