### 2.2 Patient Population

Potential trial participants will be identified at an institutional multidisciplinary tumor board, comprised of interventional radiologists, hepatobiliary surgeons, medical oncologist, and diagnostic radiologists. The potential subjects will subsequently be referred for enrollment and eligibility screening. All candidates will be reviewed for safety and eligibility by an experienced interventional radiologist, participating in the research project at each center. All eligible patients will be explained about the study protocol in details. Only those who sign the consent form will enter the trial. The inclusion and exclusion criteria are listed in **Table 2**.

**Table 2 T2:** Patients inclusion and exclusion criteria.

Inclusion criteria	Exclusion criteria
HCC diagnosed histologically or clinically according to the guidelines of the American Association for the Study of Liver Diseases tumors located immediately (<0.5 cm) adjacent to the portal vein, hepatic veins, bile duct, gastrointestinal tract, or diaphragm age ≥ 18 years no evidence of extrahepatic metastasis single tumor with a maximum diameter of ≤5cm, or the number of tumors of ≤3 and a maximum diameter of ≤3cm. Child-Pugh A or B Performance status according to Eastern Cooperative Oncology Group (ECOG) ≤2. written informed consent	Ventricular cardiac arrhythmia Congestive heart failure, NYHA Class ≥ 3 Active coronary artery disease History of epilepsy Any implanted stimulation device Other treatment <6 weeks prior to treatment presence of vascular invasion or extrahepatic metastasis. Severe coagulation abnormalities

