### 2.5 Postprocedural Follow-Up

After the procedure, all patients will be monitored for at least another day in inpatient department, in accordance with current medical practice. Routine laboratory studies, electrocardiogram, and CEUS will be performed to assess procedure-related complications.

Contrast-enhanced MRI will be performed 1 month after the procedures to evaluate technique efficacy. Complete ablation is considered complete nonenhancement of the treated tumor, and incomplete ablation is the presence of residual tumor on contrast-enhanced MRI. In the event of incomplete ablation, an additional nsPEF procedure will be conducted with the same technique. If the residual tumor is still viable after the second session, then nsPEF is considered failed, and the patient will be excluded from the trial and referred to other therapies.

If efficacy is confirmed, then clinical, biological, and radiological examinations are required every 3 months during the first year, and once every 6 months thereafter. Baseline and follow-up images will be interpreted independently by all experienced diagnostic abdominal radiologists. At the end of the trial, 2 independent radiologists will review all images before and after treatment, and reach a consensus.

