#### 2.6.2 Secondary Outcomes

The secondary outcomes are the following: technical success, technique efficacy, characteristics of the nsPEF procedure, local tumor progression (LTP), and local progression-free survival (LPFS). Specifically, technical success addresses whether the tumor is treated according to protocol and covered completely by the ablation zone; tumor coverage will be assessed immediately after the nsPEF procedure by CEUS.

Technique efficacy is regarded as radiologic complete ablation achieved after as many as 2 iterative nsPEF procedures. The nsPEF procedure characteristics include the following: number of electrodes used; active tip length of the electrodes; distance between electrodes; rate of pullback applications; total number of pulses delivered per procedure; total procedural time; ablation time; ablation volume; and sufficient ablative margin.

LTP describes the reappearance of HCC adjacent to the ablated zone after successful treatment. LPFS is defined as the time from the commencement date of the nsPEF procedure to the date of local progression. LPFS will be censored at the date of the last follow-up, when the patient has no evidence of local progression.

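### Kaplan-Meier is assigned to the cumulative incidence of local tumour progression although death without progression is a competing event, so this secondary outcome will be overstated by an amount the protocol does not let one fix

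*Protocol article*

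**What the plan says.** Section 2.8 names both the quantity and the estimator: "Survival curves and cumulative incidence of LTP will be generated using the Kaplan-Meier method". It also sets the unit of analysis: "Technical success, technique efficacy, nsPEF procedural characteristics, and local tumor progression will be analyzed per tumor". Cox models are to be used for prognostic factors, and all analyses are to be run in SPSS 23.0.

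Section 2.6.2 defines the event as local recurrence alone: "LTP describes the reappearance of HCC adjacent to the ablated zone after successful treatment". The companion outcome, LPFS, is built the same way: "LPFS is defined as the time from the commencement date of the nsPEF procedure to the date of local progression". Its censoring rule is "LPFS will be censored at the date of the last follow-up, when the patient has no evidence of local progression". Neither definition mentions death.

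Table 2 in Section 2.2 admits patients with "Child-Pugh A or B Performance status according to Eastern Cooperative Oncology Group (ECOG) ≤2". Visits under Section 2.5 run "every 3 months during the first year, and once every 6 months thereafter", with no stated end. The article does not mention competing risks.

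**The concern.** One minus Kaplan-Meier equals the cumulative incidence of an event only if nothing else can prevent that event. A patient who dies free of LTP can never have it. A liver transplant, if one takes place, has the same effect because the treated liver is removed. Kaplan-Meier can only censor such patients, and so treats them as if they would go on to have LTP at the same rate as those still followed. The resulting curve is not the proportion of tumours that will progress locally.

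Death before LTP is possible in this trial. The abstract says "Hepatocellular carcinoma (HCC) is a highly aggressive malignancy", eligibility extends to Child-Pugh B and ECOG 2, and follow-up continues past the first year. The trial has a single arm, so LTP will be read as an absolute figure, with no control group carrying the same error. At stake is the accuracy of that figure. The error makes the device look worse than it is.

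This is not a detail left to a fuller document: the article itself fixes the estimator.

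**Working it through.** **The plan's own figure.** There is none to reproduce. The article states no expected LTP rate, no death rate, no total length of follow-up and no LTP-based sample size. All rates below are therefore assumptions, shown as a range.

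**Inputs**
- Estimator: Kaplan-Meier (Section 2.8).
- Event: local reappearance only (Section 2.6.2).
- Net 1-year LTP risk p: 10%, 15%, 20% (assumed).
- Annual risk q of death without LTP: 2% to 20% (assumed).
- Horizon T: 1, 2, 3 years (assumed; Section 2.5 gives visit intervals only).

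**Formulas**, with constant cause-specific hazards a = -ln(1 - p) and b = -ln(1 - q):
- Kaplan-Meier target: 1 - exp(-aT).
- Cumulative incidence: a/(a + b) × [1 - exp(-(a + b)T)].

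**One case in full.** Take p = 15%, q = 10%, T = 2.
- a = -ln(0.85) = 0.1625 and b = -ln(0.90) = 0.1054, so a + b = 0.2679.
- One minus Kaplan-Meier: 1 - 0.85² = 27.8%.
- Cumulative incidence: (0.1625/0.2679) × (1 - 0.85² × 0.90²) = 0.6067 × 0.4148 = 25.2%.
- Overstatement: 2.6 points.

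**Across death risks, with p = 15%**

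| Annual death risk | 2 years: 1-KM | 2 years: cumulative incidence | Excess (points) | 3 years: 1-KM | 3 years: cumulative incidence | Excess (points) |
|---|---|---|---|---|---|---|
| 2% | 27.8% | 27.2% | 0.5 | 38.6% | 37.5% | 1.1 |
| 5% | 27.8% | 26.4% | 1.3 | 38.6% | 36.0% | 2.6 |
| 10% | 27.8% | 25.2% | 2.6 | 38.6% | 33.5% | 5.1 |
| 15% | 27.8% | 23.9% | 3.9 | 38.6% | 31.1% | 7.4 |
| 20% | 27.8% | 22.7% | 5.1 | 38.6% | 28.9% | 9.7 |

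(Excesses are taken before rounding.)

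At 1 year, with p = 15%, the excess is only 0.1 to 1.5 points.

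**Extremes of the whole grid**
- Smallest: p = 10%, q = 2%, T = 1 gives 10.0% against 9.9%, an excess of 0.1 points.
- Largest: p = 20%, q = 20%, T = 3 gives 48.8% against 36.9%, an excess of 11.9 points.

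**Simulation check.** Samples of 160 were drawn 2,000 times with p = 15%, q = 10% and administrative censoring uniform between 1 and 3 years. The mean 2-year estimates were 27.9% by Kaplan-Meier and 25.3% by Aalen-Johansen, in line with the closed forms.

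**LPFS.** With the same hazards applied per patient (p = 15%, q = 10%, T = 2), the definition as written targets 0.85² = 72.2% free of local progression. If death counted as an event, the figure would be 0.85² × 0.90² = 58.5%. That gap comes from the definition rather than the estimator, but its cause is the same: death has no place in either outcome.

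**The case against.** The strongest reply has four parts.

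1. **The size is unknown and may be small.** This stands. Child-Pugh B and ECOG 2 are upper limits, not the typical patient. Table 2 also admits Child-Pugh A, limits tumour number and size, and excludes vascular invasion and extrahepatic metastasis. Patients with viable tumour after two sessions leave the trial. In the 2-year case above, a rough standard error with 160 patients, one tumour each and full follow-up is √(0.252 × 0.748/160) = 3.4 points, more than the 2.6-point excess. The excess is systematic, however, and would not shrink with more patients.

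2. **One minus Kaplan-Meier is a legitimate net risk.** This stands in part. It estimates LTP risk in a hypothetical setting without death, provided death and LTP are independent. Section 2.8 promises cumulative incidence, which is a different quantity.

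3. **No sentence says that deaths are censored for LTP.** This is true. The censoring rule is written for LPFS only. But with an event that excludes death, Kaplan-Meier leaves no other way to treat a death without LTP.

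4. **The consequence is limited.** This stands. LTP is a secondary outcome, and an upward error cannot create a false claim of benefit.

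A reader might also infer that comparison with LTP rates from other series will be distorted, or that the gap becomes very large by 5 years. The documents support neither. They plan no formal LTP comparison, set no LTP threshold and do not show how outside rates were calculated. They also give no basis for a 5-year report.

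**Conclusion.** The point holds on method and direction. The estimator named in Section 2.8 does not estimate the quantity named in the same sentence, and it will overstate LTP as soon as any patient dies without it.

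The size rests on assumed rates and constant hazards: negligible at 1 year or with low mortality, a few points at 2 years with annual mortality of about 10%, and up to about 12 points at 3 years at the top of the assumed range. It would be wrong to read this as a threat to the main result, since the 1-month complete ablation rate, the adverse event rate and the sample size do not depend on it. It should be corrected before analysis because the outcome is reported as an absolute risk from a single arm and the correction is simple.

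**What to change.** In Section 2.8, estimate the cumulative incidence of LTP with the Aalen-Johansen estimator, taking death without LTP (and transplantation, if it occurs) as a competing event. Because LTP is analysed per tumour and Table 2 allows up to three tumours, obtain confidence intervals by a method that allows for clustering within patient, such as a bootstrap that resamples patients. Keep the Cox models and describe them as cause-specific.

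For LPFS in Section 2.6.2, choose one of two courses. Either count death as an event and keep Kaplan-Meier, or rename the outcome time to local progression and use the same competing-risk estimator. Without this step the same problem remains in LPFS.

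The cost is a few sentences of text, plus two practical conditions. Dates of death and of any transplant must be recorded during follow-up; the article does not list overall survival as an outcome, so this needs confirming. Section 2.8 commits every analysis to SPSS 23.0, so a second package must be named if that version lacks the procedure.

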### 2.9 Adverse Events

Device-related, periprocedural, and postprocedural adverse events will be measured using the CTCAE. Any serious adverse events will be documented in the medical records as well as in the electronic case report form and reported to the institutional review board by the responsible investigator, in accordance with the local regulations.

### 2.10 Data and Safety Monitoring Board

The DSMB will act in an independent, expert, and advisory capacity to monitor participant safety, and assess the efficacy and overall conduct of the study. The responsibilities of the DSMB are to monitor safety and efficacy data to guide recommendation for continuation of the study or early termination, and to evaluate the overall conduct of the trial. These responsibilities include monitoring: planned sample size assumptions; compliance with the protocol; recruitment figures and losses to follow-up; and continuing appropriateness of patient information. In addition, the DSMB’s responsibilities include reports on data quality and completeness of data.

### 2.11 Ethics and Dissemination

This study is conducted in accordance with the principles of the Declaration of Helsinki. The protocol has been approved by the ethics committee of all participating centers. Informed consent will be obtained from each participating patient in oral and written form. The results of this trial will be disseminated through peer-reviewed publications and conferences. Data will be available upon reasonable request.

Under these challenging inclusion criteria, our initial treatment course of nsPEF achieved 87% complete ablation based on polit data. No collateral thermal damage to the main bile duct or hepatic vascular structures were encountered. In addition, we found that nsPEF induced more slight muscle contraction than traditional IRE. Further analysis with long-term follow-up is required at the end of the recruitment.

The most important limitation of our protocol is its nonrandomized nature. However, nsPEF will be performed in only those patients with tumors close to the portal vein, hepatic veins, bile duct, gastrointestinal tract, or diaphragm (i.e., patients who are not suitable candidates for thermal ablation and surgery). Since these later methods would predictably fail for patients in this study, we favored a single-arm study design with an effectiveness threshold. Along with the scientific and deeper understanding for pathophysiology mechanism of HCC, recent researches have revealed the role of BRAF in HCC, which long non-coding RNA of BRAF may be another mechanism of cancer proliferation and tyrosine kinase inhibitors escape in HCC (39). Targeted therapy combinations, including BRAF pathway, may bring light in new treatment of HCC. With initial promising results of this study, further relevant studies would be useful, such as nsPEF treatment compared to targeted therapy, or nsPEF combined with multi-pathways inhibition therapy. These exploring studies may open the door for better results in the treatment of HCC.

In summary, this study is the first-in-human trial to evaluate the efficacy and safety of nsPEF in patients with HCC who are considered unsuitable for thermal ablation. The design of the trial and its primary, secondary, and exploratory endpoints have the potential to broaden our understanding of electroporation-based technologies in medicine, and provide new minimally invasive therapeutic pathways for HCC at high-risk locations.

## Data Availability Statement

The raw data supporting the conclusions of this article will be made available by the authors, without undue reservation.

## Ethics Statement

The studies involving human participants were reviewed and approved by First Affiliated Hospital of Zhejiang University, First Affiliated Hospital of Zhengzhou University, Shulan Hospital, and First Affiliated Hospital of Xinjiang Medical University. The patients/participants provided their written informed consent to participate in this study.

